### Objectives (7)

The primary study objective is to compare the effectiveness of on-site integrated care that includes adherence counseling vs. off-site referral to care with support of a patient navigator in increasing rates of (1) PrEP adherence (0–6 months) and (2) HCV sustained viral response 12 weeks post-treatment completion (SVR12) among PWID recruited in OAT and SSP in Miami, FL, and Montreal, Quebec. The study will examine the relative contributions of living in cities with different healthcare systems (Miami vs. Montreal) and venues (OAT vs. SSP) on primary outcomes.

Secondary objectives are to measure differences between study arms in (1) PrEP initiation, (2) long-term sustained PrEP adherence (6–18 months), (3) HCV infection/reinfection, (4) sexually transmitted infections and reinfection (including HIV), and (5) behavioral disinhibition, i.e., the proportion of participants who increase sexual or injection risk behaviors.

The study will include a qualitative component with the following objectives: (1) to explore individual and structural factors influencing PrEP initiation and adherence; (2) to examine how PWID understand and define PrEP adherence; (3) to describe and understand PWID’s experience regarding on-site and off-site interventions including their perceived effects on PWID’s health; (4) to examine if and understand how PrEP use is related to HIV risk behavior modifications among PWID; (5) to understand facilitators and barriers to implementation and how study staff experience and address these factors during the trial.

Finally, a cost-effectiveness analysis will evaluate (1) healthcare services utilization and cost-effectiveness of the on-site integrated care approach compared to the referral with patient navigator and (2) the healthcare resources required to scale up these intervention approaches in the local environments and site settings.

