### Outcomes (12)

#### Primary outcome measures

The co-primary trial outcomes are (1) sustained PrEP adherence during the first 6 months and (2) HCV cure among participants living with HCV.

**Table 4 Tab4:** Definition and measure of secondary and tertiary outcomes

Secondary outcomes	Definition	Measure
PrEP initiation/uptake	Receiving a prescription and taking the first dose of the medication	First dose of Rx dispensed to the patient and recorded at pharmacy/dispensing venue + self-report
Long-term sustained PrEP adherence	PrEP use at 6, 12, and 18 months post-randomization	Self-report + detectable level of TDF in DBS 6, 12, and 18 months post-randomization
HCV incidence/re-infection	New HCV infection	At scheduled visit: HCV-Ab positive (never infected) or detectable HCV-RNA (previously infected and cured)
STI or HIV incidence/STI re-infection	New STI or HIV infection in a previously uninfected person/previously infected and cured person	At scheduled visit: Any positive test result for *Neisseria gonorrheae*, *Chlamydia trachomatis*, syphilis, or HIV
Behavioral disinhibition	Changes or increase in sexual or injection risk behaviors	Self-report at each visit
**Tertiary outcomes**	**Definition**	**Measure**
Ongoing PrEP use	Any PrEP use during any period	Any detectable level of TDF in DBS/Self-report of use
HCV SVR within those initiating	12-week sustained viral response post-end of treatment	First dose of medication dispensed to the patient and recorded at pharmacy/dispensing venue + self-report/HCV-RNA negative at 12 weeks post end of treatment

Sustained PrEP adherence will be compared between both treatment arms at 6 months post-randomization. Sustained PrEP adherence will be defined as the self-report of achieving daily PrEP use, which will be confirmed by evidence of detectable levels of tenofovir. In order to achieve protection against HIV infection, TDF/FTC should be taken once daily to achieve protective levels. PrEP use will be self-reported by participants. Blood tenofovir will be detected using DBS collected every month beginning at 8 weeks post-PrEP initiation during the first 6 months post-randomization and subsequently every 3 months during research visits.

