We will analyze long-run sustained PrEP adherence and HCV cure resulting from treatment initiated after the first 6 months, similarly, except using a repeated-measures Poisson regression implemented as a generalized estimating equation (GEE) including the periods between 6- and 18-month follow-ups. It is important to note that for all PrEP adherence analyses, any participants who become HIV positive will be counted as PrEP non adherent. For all other secondary outcomes, similar approaches will be used. PrEP initiation will be assessed as a simple binary outcome (initial self-reported use verified by prescription in medical records) and again modeled using repeated measures Poisson regression. We will examine sustained PrEP adherence among those self-reporting taking PrEP to disentangle PrEP non-engagement, inadequate PrEP use, and protective levels of PrEP use. Note that protective levels of PrEP use will be examined only among patients not on HCV medication due to norms for protective PrEP use when taken with HCV medication not having been established. We will examine HCV treatment initiation and rates of SVR among those treated (the primary analysis will include all HCV-positive randomized participants). We will examine potential rates of behavioral disinhibition as measured by changes in self-reported sexual risk (i.e., condom-less vaginal and/or anal sex), needle/works sharing, HCV infection/re-infection rates, and STI (including HIV) infection rates over the entire follow-up period. Additional analyses will examine the timing of initiation of both PrEP and HCV treatment, and whether non-engagement and discontinuation of PrEP are related to levels of (or changes in) risk.

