## Discussion

Despite the on-going HIV epidemic among PWID, there has been little PrEP implementation research among this population [104]. Numerous groups have cited the need for more research on PrEP with PWID [32, 104, 105] and specifically research on how to optimize different HIV preventive interventions and bring them to scale for PWID [22]. Although PrEP awareness might be increasing, uptake remains low. Studies from 2015 to 2016 reported awareness of 12.4–24% and uptake of 0.7–2.6% [106, 107]. In contrast, in a survey of 397 PWID from San Francisco performed in 2018, 56.7% were aware of PrEP, but only 3.0% had used it in the last 12 months [108]. The qualitative component of our study will explore barriers and enablers as perceived by patients and staff regarding PrEP initiation and adherence. Our study’s innovation is further supported by our ability to provide new and critical data on the eligibility, uptake, and adherence of PrEP among PWID in two very different environments. While prior studies have analyzed the uptake and cost-effectiveness of PrEP among MSM [109–111], more research is needed on the implications of expanding PrEP to PWID.

Minimal research has been conducted regarding the association between PrEP use and HCV infection and/or re-infection and consists mainly of case series. This is in contrast to multiple studies examining the association of PrEP with bacterial STI risk [112–114]. Better understanding of HCV infection and reinfection rates in this population has key implications for policy and clinical care. HCV incidence is also an excellent quantitative measure of injection risk of blood-borne viral acquisition.

This trial represents a novel opportunity to assess the incremental health benefits and costs of an integrated HIV and HCV care model for PWID. It will allow us to use cutting-edge techniques to jointly simulate the impact of preventing and curing multiple comorbid conditions affecting PWID using data collected in a single clinical trial, whereas in the past our models have relied primarily on data collected for single conditions even when we seek to forecast multiple disease outcomes.

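### Section 20a lists HIV infection rates among the measures of behavioral disinhibition, although PrEP lowers HIV without any change in behavior and Table 4 measures disinhibition by self-report

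*Protocol article*

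**What the plan says.** Objectives (7) lists HCV infection, STI including HIV, and behavioral disinhibition as three separate secondary objectives (3, 4 and 5). It explains the last as "the proportion of participants who increase sexual or injection risk behaviors".

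Table 4 under Outcomes (12) agrees. It defines disinhibition as "Changes or increase in sexual or injection risk behaviors" and gives self-report at each visit as the only measure. HCV infection has its own row. HIV shares a row with bacterial STIs, defined as "New STI or HIV infection in a previously uninfected person/previously infected and cured person" and measured by a positive result on any of four tests: gonorrhea, chlamydia, syphilis or HIV.

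Statistical methods (20a) differs: "We will examine potential rates of behavioral disinhibition as measured by changes in self-reported sexual risk". The same list goes on to sharing of needles or works, then HCV infection and re-infection rates, and ends with "STI (including HIV) infection rates over the entire follow-up period".

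On the drug itself, Outcomes (12) states: "In order to achieve protection against HIV infection, TDF/FTC should be taken once daily to achieve protective levels".

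**The concern.** One secondary outcome has two measures that do not match. In Objectives (7) and Table 4 it is a reported behavior. In section 20a it is reported behavior plus laboratory infection rates.

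The mismatch matters most for HIV. A marker of risk behavior should move only when behavior moves. HIV incidence also moves with PrEP use, and the trial is designed to show that PrEP use differs by arm. If HIV counts as a disinhibition measure, the arm with better adherence looks less disinhibited for a reason unrelated to behavior.

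A related ambiguity sits in Table 4 and objective 4. HIV is the infection that PrEP is offered to prevent, yet the text does not settle whether its incidence is shown by arm or only together with bacterial STIs, which would probably be far more frequent.

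**Working it through.** The plan gives no figure on this point and no infection rates. The check is a comparison of texts, followed by bounds on stated assumptions.

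**1. Texts side by side**

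| Place | Disinhibition measured by |
|---|---|
| Objectives (7), objective 5 | proportion increasing risk behavior |
| Table 4 | self-report at each visit |
| Section 20a | self-reported sexual risk, sharing of needles or works, HCV rates, STI rates including HIV |

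The first two agree. The third adds infection rates.

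**2. How far HIV could differ with identical behavior**

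Sample size (14) plans 40% vs 55.5% adherence. As a check on that input, 250 per arm at two-sided alpha 0.025 gives power 0.893, matching the stated 90%. Take the bounding case: full protection in adherers, none in others, and 6-month adherence held for 18 months.

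- HIV rate ratio, on-site to off-site = (1 − 0.555)/(1 − 0.40) = 0.445/0.60 = 0.742.
- Rise in on-site exposure needed before HIV rates become equal = 1/0.742 − 1 = 35%, if HIV risk is proportional to exposure.

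**3. Effect on a pooled STI/HIV rate**

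Assumed off-site rates per 100 person-years: HIV 1 to 2, bacterial STI 10 to 30, with STI equal in both arms. HIV is then 1/31 = 3.2% to 2/12 = 16.7% of events. Person-time is 250 × 1.5 = 375 years per arm with no loss.

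- Pooled ratio = (0.742 × HIV + STI)/(HIV + STI).
- 95% factor = exp(1.96 × √(1/a + 1/b)), where a and b are the event counts.

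| HIV, STI | Pooled ratio | Events, off-site vs on-site | Factor | 95% limits |
|---|---|---|---|---|
| 2, 10 | 0.957 | 45.0 vs 43.1 | 1.52 | 0.63 to 1.45 |
| 1, 10 | 0.977 | 41.2 vs 40.3 | 1.54 | 0.63 to 1.51 |
| 2, 30 | 0.984 | 120.0 vs 118.1 | 1.29 | 0.76 to 1.27 |
| 1, 30 | 0.992 | 116.2 vs 115.3 | 1.29 | 0.77 to 1.28 |

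The shift is 0.8% to 4.3%. With 20% of person-time lost (assumed; 300 years per arm) the factor widens to between 1.33 and 1.62.

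**4. What a separate HIV result could show**

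Off-site 3.75 to 7.5 infections and on-site 2.8 to 5.6, in total 6.5 to 13.1 (5.2 to 10.5 with 20% loss). Four events in 375 person-years give 1.07 per 100, exact 95% CI 0.29 to 2.73. Over a wider assumed range of 0.5 to 4 per 100 in both arms, 750 person-years give 3.75 to 30 events, and power for a halved hazard at two-sided 0.05 is about 10% to 48%. Such a result is descriptive.

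**5. HCV re-infection**

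Table 4 counts re-infection only in people previously infected and cured. Sample size (14) plans cure in 40% vs 63% of about 240. With 120 per arm (assumed equal split), 0.40 × 120 = 48 and 0.63 × 120 = 75.6 people are newly at risk. With the same re-infection risk per cured person, on-site counts would be 75.6/48 = 1.58 times the off-site counts. That bias runs opposite to the one for HIV. Rates per person-time at risk correct the denominator, but not the fact that those at risk were selected after randomization by treatment success.

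**The case against.** The section 20a sentence can be read as three separate things to examine: disinhibition by self-report, HCV rates, and STI/HIV rates. That would match objectives 3 to 5 and Table 4, and it is the only sentence there that names these infection rates. This reading is possible, but the phrase *as measured by* in front of a single list makes the other one more natural. The text is at best ambiguous, and the same edit cures it.

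An open-label trial has good reason to set objective markers beside self-report. That stands, and it is why bacterial STI and HCV incidence should stay. The Discussion supports the latter: "HCV incidence is also an excellent quantitative measure of injection risk of blood-borne viral acquisition".

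A reader might infer from Table 4 that HIV is buried in a composite. The document does not show that. The row title limits re-infection to STI, nothing calls the row a composite or a time to first event, and it can be read infection by infection. How a row is tabulated is also commonly left to the analysis plan, which is not shown. Only a request for clarification remains.

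A reader might also infer that HIV is the only flawed item and that HCV rates are free of the problem. That is unsafe for re-infection, because its risk set depends on a co-primary outcome planned to differ by arm. The Discussion's general support for HCV incidence does not remove that dependence.

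**Conclusion.** The point holds as a minor correction. Section 20a, most naturally read, measures disinhibition differently from Objectives (7) and Table 4. HIV is an unsuitable item on its list, because the planned adherence difference can separate HIV rates with no difference in behavior. HCV re-infection needs care for a different reason.

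The size is small. A reader might infer that a pooled result would be materially distorted, but the bounds do not support that: the shift is well inside sampling error on every assumed pair of rates. The 35% exposure figure is a best-case ratio for HIV alone and rests on few expected events. All infection rates here are assumptions, as are constant adherence and all-or-nothing protection. HIV protection is not a stated hypothesis, and the co-primary results, alpha and sample size are unaffected. The gain is a consistent definition and an HIV result that can be read by arm.

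**What to change.** - **Section 20a:** state that self-reported change in sexual or injection risk behavior defines disinhibition, as in Table 4. Remove HIV from its measures. Keep bacterial STI and HCV incidence as supportive markers. Give HCV re-infection per person-time at risk after cure, with a caution that this group is selected by treatment success.
- **Table 4 and objective 4:** separate HIV incidence from bacterial STI incidence and re-infection. Report HIV by arm as events, person-years and rate with exact 95% confidence interval, labelled descriptive.

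No new data are needed, since HIV is already tested in all participants every 3 months (sections 11b and 18a). The cost is a few edits and one more imprecise descriptive row.

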#### Secondary and tertiary outcomes measures

Secondary and tertiary outcomes measures are presented in Table 4.

### Participant timeline (13)

The participant timeline is presented in Fig. 1.

### Sample size (14)

We will utilize an alpha of .025 to account for our two co-primary outcomes. Our sample will include 500 participants in the PrEP component and approximately 240 in the HCV component. We estimated power using a simulation program written for SAS 9.4. This program generated data with various constellations of treatment effects, site effects, venue effects, and interactions. A simple power analysis shows that with 500 participants and alpha = .025 that there is 90% power to uncover an absolute difference of approximately 15% (40% versus 55.5%, RR = 1.40) for main effects of the treatment arm (across site and venue). This power statement assumes that response rates are at the point of highest variance in the binomial distribution—i.e., variance decreases causing power to increase if the probabilities are actually further from .5 in either direction. We anticipate larger absolute differences but have kept the simple power high to account for the potentially complex interactions we might see. For example, with this sample size, the power for the primary (PrEP) outcome is about 86.8% when there are differences in site and venue of 13% and 16% respectively, and when power for the site and venue differences is greater than 80%. There is better than 80% power for an interaction effect (e.g., site by treatment) with a rate ratio [RR(site 1)/RR(site2)] of at least 1.37. Power for effects within a site or venue is around 90% for an absolute risk difference of .22 (40% versus 62%). Note that planned tests of differences (i.e., interactions) by the biological variable, sex, would need to have a rate ratio of 1.5 to have 80% power. For HCV outcomes, the sample size is expected to be smaller (*n* = 240); for the HCV primary hypothesis, there is 90% power to uncover an absolute difference of 21% (40% versus 63%, RR = 1.58), well within the range of what we expect for this intervention [63]. This is based on the extremely low rates of PrEP currently in our candidate venues and the relatively high rate of continuation (58%) in the open-label extension of the Bangkok Tenofovir Study where PrEP was provided without cost as is the case in the current protocol [63].

### Recruitment (15)

To achieve a sample size of 500, approximately 720 potentially eligible individuals from the Miami and the Montreal sites will be invited to participate. Initially, each site was supposed to screen approximately 120 individuals every 6 months. The COVID-19 pandemics significantly affected recruitment (see specific section) and recruitment is now expected to be completed in Fall 2022.

Participants will primarily be recruited through the participating SSP and OAT clinics. Study sites have been consulted to establish the best method of informing their patients about the project and inviting potential participants to meet with study staff to determine their eligibility. Individuals interested in participating who are not patients at study SSP or OAT sites must first become patients of those sites to participate. Individuals who are not interested in hearing more about the study are noted in a recruitment ledger so the number of approaches made during the selected recruitment time can be calculated.

## Assignment of interventions: allocation

### Sequence generation (16a)

Participants are randomized to one of two treatment groups in a 1:1 ratio. Randomization at the individual level uses a permuted-block randomization scheme to ensure relative balance across time; the block size is randomly permuted to prevent study staff from guessing the block size and inferring the condition to which the next participant will be assigned. Randomization tables have been generated by study statisticians separately for venues within site and by HCV antibody status.

### Concealment mechanism (16b)

Randomization is handled centrally and administered via the Research Electronic Data Capture (REDCap) system to conceal the randomization process and group assignments until they are assigned.

### Implementation (16c)

The statistician generates the allocation sequence and this is encoded into the REDCap system. The study coordinator enrolls individuals into the study for assessment of inclusion-exclusion criteria. When the inclusion-exclusion variables have been determined and entered into the REDCap system, the condition assignment is generated.

## Assignment of interventions: blinding

### Who will be blinded (17a)

This trial is an open-label, un-blinded study. Given the pragmatic nature of the trial, participants, providers, and research staff are not blinded. Research and clinical staff are blinded to the randomization procedure to prevent predictions about participant assignment. Research and clinical staff are initially blinded to arm assignment to avoid bias, but after baseline, the research and clinical staff are not blinded.

Regarding data analysis, analysis strategies are pre-specified, and complete statistical analysis plans will be finalized prior to the data being locked. Whereas the data analysts will not be blinded because the same staff is performing data management, the study investigators including the study statistician ([name]) will be blinded to treatment assignment until results are finalized.

### Procedure for unblinding if needed (17b)

Not applicable, see 17a

## Data collection and management

### Plans for assessment and collection of outcomes (18a)

Data collection is planned at screening, baseline, and every 3 months thereafter. “Full” research follow-up visits occur at approximately 6, 12, and 18 months post-randomization while participants have short interim research visits approximately 3, 9, and 15 months post-randomization. In the first 6 months post-randomization, participants are scheduled for DBS monthly after 8 weeks of initiating treatment if on PrEP. Pregnancy tests will be required at each research visit for all randomized participants of child-bearing potential. Tables 2 and 3 describe the battery of assessments and lab assessments planned.

Assessments are administered in a private space by a trained interviewer through a computer-assisted personal interview (CAPI) or through paper case report forms (CRF) that are later entered into an electronic data capture (EDC) system. Self-report questionnaires are programmed in REDCap and administered from a password-protected website. Wherever possible, we use measures from NIDA’s Data Harmonization projects (e.g., Seek, Test, Treat and Retain [64]) or established PrEP studies (e.g., the PrEP Demo Project) [65]. Assessments are interviewer-administered; the initial assessment will take approximately 90 min and others 45–50 min.

#### Assessment of outcomes

For participants initiating PrEP, adherence verification by self-report and DBS collection begins 8 weeks post-PrEP initiation and is performed once a month thereafter for the first 6 months post-randomization and then at 3-month intervals until the end of the study.

For HCV-treated patients, HCV RNA is tested 12 weeks after treatment initiation (end of treatment), at SVR (12 weeks post-treatment completion/discontinuation), and at 3-month intervals thereafter to detect reinfection.

HIV, syphilis, chlamydia, gonorrhea, and HBV (if non-immune) testing are performed on all participants at 3-month intervals. New HCV infections are detected at 3-month intervals: HCV RNA testing is done on participants who were HCV Ab reactive and HCV RNA negative at their previous visit and HCV Ab testing is done on participants who tested HCV Ab negative at their previous visit (Table 2).

